### Concealment mechanism {16b}

The Clinical Epidemiology and Biometry Unit staff generating the randomization list will serve as the unblinded team, responsible for generating and also storing the randomization list and for communicating with other co-investigators or with ME/placebo suppliers if necessary. ME/placebo will be kept in anonymous vials, bearing alpha-numeric codes, lot numbers, and expiration dates. These vials will be logged and stored in a locked room at each NICU.

### Implementation {16c}

The local study coordinator, after checking patient’s eligibility and randomization list, gives the appropriate bottle of drops to the neonatologist. Each bottle will be labeled “A” or “B” and will also indicate the patient’s identity, the date of the first administration, and the batch number.

## Assignment of interventions: blinding

### Who will be blinded {17a}

With the exception of the staff of the Unit of Clinical Epidemiology and Biometry at the coordinating center, the entire study staff (health care professionals, outcome assessors and data analysts) will be blinded, as will each participant’s parents. The Unit of Clinical Epidemiology and Biometry will be responsible for unblinding in case of necessity (severe AEs possibly related to intervention).

### Procedure for unblinding if needed {17b}

Unblinding will be performed on completion of the study. Under normal circumstances, all participants will be unblinded simultaneously once the database is complete. Urgent, unplanned unblinding prior to this point will be done if needed to ensure participant safety, e.g., to identify the drug involved during an acute reaction. Unblinded information will be shared only on a need-to-know basis.

## Data collection and management

### Plans for assessment and collection of outcomes {18a}

All the trial staff members are well trained in protocol procedures and requirements of Good Clinical Practice (GCP), Good Laboratory Practice, and Good Experimental Practice guidelines and have already worked on clinical trials; moreover, the trial will be monitored, throughout its course, by the coordinating center’s ethics committee quality assurance team (ECQT). All staff members involved in the study are part of a clinical team that routinely takes care of preterm infants from 23 weeks of GA. Every operator involved in outcome evaluation has consolidated experience in the use of the chosen tools and has undergone specific training, when required (e.g., for assessment of GMs or for performing the NAVEG protocol for assessment of visual abilities). All the tests, procedures, and clinical evaluations that will be performed are validated. In the following paragraph, all the assessments to be used for collection of the outcomes are detailed and supported by the relevant references, confirming their validation and current use.

#### Experimental design aim 1

In accordance with the study’s double-blind, parallel-arm design, a total of 60 preterm newborns with GA ≤ 29 + 6 (weeks+days), if able to receive 20 ml/kg/day enteral feeding within 96 h of birth, will be randomly assigned to receive 3 mg/kg/day ME drops, or the equivalent amount of placebo drops, for 15 days. At the end of the 15 days, we aim to assess differences in plasma concentrations of MDA and ME in the supplemented vs the not supplemented group and vs the baseline situation.

At recruitment and then after 15 days of treatment, 250 μl plasma samples will be obtained from 500 μl neonatal blood samples by means of ethylene-diamine-tetra-acetic acid. These plasma samples will be used to measure MDA concentration (nmol/ml), by high-performance liquid chromatography (HPLC, Chromsystems Instruments & Chemicals; Grafelfing/Germany), and ME concentration (pg/ml), quantified in one chromatographic run by HPLC with fluorimetric detection [31] (a LC-10AD pump, an RF-551 fluorescence detector, and a SIL-10AD autosampler, Shimadzu Italia, Italy).

All the measurements will be performed at the coordinating center’s Clinical Chemistry Laboratory (Fondazione IRCCS Policlinico San Matteo, Pavia, Italy).

#### Experimental design aim 2

Obstetric and perinatal data will be recorded for each infant according to the Vermont Oxford Network criteria [32]. Moreover, at TEA (40 weeks), clinical and instrumental outcomes will be evaluated by collecting/performing the following:
Anthropometric measurements;Incidence and grade of ROP, measured by indirect ophthalmoscopy (Ophthalmic Imaging System, RetCam 3, Clarity Medical Systems, Pleasanton, CA, USA);Incidence of hearing abnormality, evaluated with brainstem auditory evoked responses (Otodynamics Audiology Systems, Hatfield, Herts, UK);Incidence and severity of infection/sepsis;Incidence and severity of BPD;Results of neurological examination, conducted according to the Amiel-Tison method [25];Assessment of GMs [26];Assessment of visual behavior, performed using a new standardized tool (NAVEG) and investigating different aspects of neonatal visual function [27];Administration of the Neonatal Intensive Care Unit Network Neurobehavioral Scale [33];cUS findings: PVH/IVH as classified by Papile [23], PVL as classified by de Vries [24], and ventricular dilatation according to Ment [34] (Ultrasound model: Hitachi ALOKA Arietta V70, Hitachi Medical Systems Europe Holding AG, Zug, Switzerland, www.hitachi-medical-systems.com). cUS findings will also be classified and grouped according to Rademaker [35];Brain MRI during spontaneous sleep, performed using a 1.5-Tesla MRI scanner (Siemens) by radiographers blinded to participant allocation to the placebo or ME group; qualitative and quantitative volumetric techniques will be used to estimate overall and regional brain volumes for different tissue types; diffusion tensor imaging will be used to evaluate the integrity and maturation of WM by apparent diffusion coefficient and fractional anisotropy. Harmonization of scans at the different centers will be guaranteed.Parental stress assessment with validated surveys, as a control factor, in order to take into account the influence of parental stress on the children’s development [33]. This will be done by administering the Parental Stressor Scale: Neonatal Intensive Care Unit, the Modified Perinatal Post-traumatic Stress Disorder Questionnaire, the State Anxiety Inventory, and the Edinburgh Postnatal Depression Scale. All the surveys are validated and will be administered by trained personnel.

#### Experimental design aim 3

At 4–6 months of CA, we will collect/perform the following:
Anthropometric measurements;Neurological examination;The modified Fagan Test of Infant Intelligence [22], which is moderately predictive of later cognitive abilities. The test will be carried out using an innovative new method involving automated eye tracking (Tobii TX 300, Tobii AB, publ, Danderyd, Stockholm, SE. https://www.tobiipro.com), aimed at ensuring accuracy and objectivity. The first target is novelty preference, which is the proportion of time the infant spends looking at a novel stimulus compared with the time spent looking at a previously presented stimulus. The second target is fixation duration, i.e., the mean duration of gaze at a stimulus.

At 18–24 months of CA, neurodevelopmental outcomes in the two groups will be evaluated through:
Anthropometric measurements;Neurological examination;Standardized developmental assessment, performed using the Griffiths Scales of Child Development 3rd Edition [28];The CBCL, a self-administered survey completed by parents [29].

### Plans to promote participant retention and complete follow-up {18b}

The trial staff will be responsible for follow-up of patients. At the first follow-up (40 weeks of GA), the patients will mainly still be hospitalized. Subsequent follow-up visits will be planned with parents. In order to encourage compliance with the scheduled assessments, the study coordinator will telephone parents a week before each scheduled assessment. Parents will also be telephoned, with a reminder, should patients miss an appointment.

### Data management {19} and confidentiality {27}

All study-related information will first be collected in case report forms (CRFs) and then entered into the database by dedicated members of the trial staff. All collected data will then be stored securely at the coordinating center. Double-data entry by dedicated personnel will ensure correspondence between CRF and database data. The data value ranges used in the study will be those for preterm infants, checked by a neonatologist and by the data manager at the coordinating center. All participant information will be stored in locked filing cabinets in secure rooms accessible only to designated study staff (PIs, co-investigators, data analysts). All records that contain names or other personal identifiers will be stored separately from study records, anonymized and protected by an identification code which may be accessed only by authorized personnel. The participants’ study information will not be released outside the context of the present study without the written permission from the participant (parents).

### Plans for collection, laboratory evaluation, and storage of biological specimens for genetic or molecular analysis in this trial/future use {33}

Not applicable as no biological specimens for genetic or molecular analysis will be collected as part of this trial.

## Statistical methods

### Statistical methods for primary and secondary outcomes {20a}

With regard to analysis of the trial results, a normality test (Shapiro-Wilk test) will be used to determine whether datasets are well modeled by a normal distribution. Categorical variables will be described as counts and percentages and compared between treatment groups by chi-squared test or Fisher’s exact test. Continuous variables will be expressed as mean and standard deviation or median and interquartile range, and comparisons between treatment groups will be made using the *t*-test for independent groups or an analogous non-parametric test if the variable is not normally distributed. Potential multivariate analysis will be performed with regression models. To account for non-independence of observations in case twins are enrolled, general estimating equations (GEE) or mixed regression models will be used. Statistical analysis will be performed by the Clinical Epidemiology and Biometry Unit at the coordinating center using the STATA statistical package (Stata, release 16 or later, StataCorp, College Station, TX, USA).

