### Trial design {8}

The planned study will have a superiority, prospective, multicenter, parallel-groups, randomized, double-blind vs placebo-controlled design. Participants will be randomly allocated to the intervention group or the control group, in a 1:1 ratio. The intervention period will last 15 days. Preterm comorbidities and neurodevelopmental outcome will be evaluated throughout the first 24 months of CA. Table 1 shows the assessments to be administered at baseline and immediately post-intervention. This trial protocol is designed in accordance with the Standard Protocol Items: Recommendations for Interventional Trials (SPIRIT) 2013.

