### Sample size {14}

The literature contains only one paper sufficiently similar to our study [30]; this paper was taken as a reference source to select the primary outcome (MDA concentration in the two groups) and calculate the sample size for our proposed study. A total of 26 patients per group is deemed sufficient to detect, with a power greater than 80%, a statistically significant difference equal to 8 nmol/ml (standard deviation in the two groups equal to 7) between the null hypothesis (H_0_) of the same concentration of MDA 16 nmol/ml in the two groups and the alternative hypothesis (H_1_) of an MDA concentration reduction to 8 nmol/ml in group 2 (*t*-test for independent groups with alpha error = 5%). Considering a potential dropout rate of 15%, 30 newborns per group will be enrolled.

All the participating patients will be enrolled by the two participating NICUs.

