## Assignment of interventions: allocation

### Sequence generation {16a}

The randomization will be generated by the Unit of Clinical Epidemiology and Biometry (unblinded team) at the coordinating center, according to a 1:1 allocation ratio, by means of computer-generated random numbers that will allow for extra patient allocations in the event of dropouts. The randomization sequence will be generated by a random number generator at the same unit. The PIs of the two NICUs will sequentially allocate the participants to the two groups on the basis of the generated lists.

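### If twins are enrolled, the primary MDA test switches to GEE or a mixed model as if the two were equivalent; in a trial of this size that could raise the 5% error rate to about 6–14%

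*Protocol article*

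**What the plan says.** Sample size {14} of the protocol article bases the primary comparison on a t-test "for independent groups with alpha error = 5"%. It assumes MDA of 16 versus 8 nmol/ml and a standard deviation of 7, with 26 infants per group. It then states: "Considering a potential dropout rate of 15%, 30 newborns per group will be enrolled".

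Statistical methods {20a} gives the t-test, or a non-parametric analogue, as the standard comparison for continuous variables. It then adds a rule for twins: "To account for non-independence of observations in case twins are enrolled, general estimating equations (GEE) or mixed regression models will be used". The rule is not limited to secondary outcomes, so it covers MDA. The section does not give the working correlation, the type of standard error, ML or REML, the reference distribution or the expected number of twins.

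Sequence generation {16a} says: "The PIs of the two NICUs will sequentially allocate the participants to the two groups on the basis of the generated lists". It has no rule for twins, so individual allocation is the natural reading.

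**The concern.** The twin rule is there to protect the error rate. In this setting it may do the opposite. Most of the 60 infants will presumably be singletons, so the within-pair correlation would be estimated from a handful of pairs. When chance makes that estimate too high, the few pairs split between the arms get very large weight, and the standard error comes out too small. Large-sample tests from GEE, or from an ML or REML mixed model, make no allowance for this.

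The two named methods also do not behave alike here. With both left open for the primary test, the error rate depends on a choice the protocol does not make and that could be made after results are seen. At stake is whether a positive MDA result carries the stated 5% error, and whether its confidence interval is wide enough. Other continuous outcomes are affected in the same way.

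**Working it through.** **Inputs from the protocol.** Alpha 5% (two-sided assumed, as sidedness is not stated), difference 8, SD 7, 26 per group analysed and 30 enrolled, 1:1 allocation. The analysed total is therefore taken as 52 to 60.

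**Inputs assumed.** Number of twin pairs and within-pair correlation. The full grid was 2–12 pairs and correlation 0–0.8.

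**The plan's own figure.** n per group = 2(1.96 + 0.84)² × (7/8)² = 12.0, so 13 per group (14 with the t distribution) for 80% power. The stated 26 is not the minimum for 80%. It gives about 98% power, so the claim of more than 80% is literally true. Enrolment: 26 × 1.15 = 29.9, so 30.

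**Why the t-test survives individual allocation.** If infants are randomised singly and treatment has no effect, the randomisation variance of the mean difference is S²(1/n₁ + 1/n₀), whatever the correlation between siblings. The t-test estimates this quantity.

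**Why the model-based tests do not.** Take 60 infants with 7 pairs.
- There are 60 − 14 = 46 singletons. With 23 per arm, their information on the treatment effect is 23/(2σ²) = 11.5/σ².
- The chance that a pair is split between arms is 30/59 = 0.51, so about 7 × 0.51 = 3.6 pairs are split.
- A split pair has information 1/[2σ²(1 − ρ)]: 0.5/σ² at ρ = 0, 1/σ² at ρ = 0.5 and 10/σ² at ρ = 0.95.
- If ρ is estimated at 0.95, three split pairs contribute 30/σ², more than twice the 11.5/σ² from all 46 singletons.

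**Simulated type I error.** Null normal outcomes, 5,000–8,000 trials per setting, nominal 5%. The Monte Carlo standard error is at most √(0.05 × 0.95/5,000) = 0.3 percentage points at 5%.

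| Analysis | Twins allocated individually | Twins allocated together |
|---|---|---|
| t-test ignoring twins | 4.2–5.6% | up to 8.9% |
| Exchangeable GEE, model-based z | 7.4–14.3% | see below |
| Exchangeable GEE, sandwich z | 7.0–11.6% | see below |
| Mixed model, ML, z (8–12 pairs if individual) | 6.2–9.5% | 4.9–7.2% |
| Mixed model, REML, z (8–12 pairs if individual) | 5.8–8.7% | 4.6–6.5% |
| Independence GEE, sandwich z | 5.3–7.2% | not reported |

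With twins allocated together, exchangeable GEE gave about 6–8% at correlation 0.3 or more (up to 8.7% with 2 pairs), and up to 12.5% with 2 pairs and zero correlation.

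A separate simulation with individual allocation, 3–10 pairs and correlation 0.2–0.7 (6,000 runs per setting) gave ML z 7–10% and REML z 7–9%. With fewer than 8 pairs the full grid went higher, to 18.9% for ML and 15.0% for REML. Those extremes are not used in the conclusion.

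**Checks on the cause.**
- With the true correlation supplied, GEE falls to 5.4–7.1%. The excess therefore comes mainly from estimating the correlation.
- Much of the upper range comes from trials where the estimated correlation reaches its limit (set at ±0.95). Example with 60 infants, 5 pairs and correlation 0.5: 17.1% of trials reach it, and GEE gives 13.4% (model-based) and 9.5% (sandwich). Without those trials the figures are 7.4% and 7.1%.
- A packaged GEE routine with 60 infants, 7 pairs and correlation 0.5 gave 15.8% (model-based) and 13.3% (sandwich), against 5.2% for the t-test. Its fits often hit the iteration limit, so the exact size depends on the software. Stata itself was not run.

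**Candidate remedies, individual allocation.** REML with Kenward-Roger gave 4.5–5.5% (3–10 pairs, correlation 0.2–0.7). A randomisation test re-allocating infants individually gave 4.7–4.8% (5 or 8 pairs, correlation 0.5). Replacing z by a t reference with clusters minus 2 degrees of freedom is not enough: REML gave 5.2–8.0% at 8–12 pairs, and sandwich GEE gave 6.1–8.9%.

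**The case against.** The strongest reply is that the faulty step is not in the document. Statistical methods {20a} names two model families and no z test. REML with Kenward-Roger is a mixed regression model and is available in Stata, so the recommended analysis already fits the sentence. Degrees of freedom, standard errors and working correlation are commonly left to an analysis plan, which is not shown here. All of that stands, and the missing detail is not itself an error. What remains is that the protocol treats GEE and a mixed model as equivalent for the primary test, although exchangeable GEE inflates the error most at this size.

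A reader might infer that the twin rule would raise the error rate to 8–14% as a matter of course. The documents do not support that. The rule applies only if twins are enrolled, the number of pairs and the correlation are assumed, and independence GEE with sandwich errors stays at about 5–7%. The upper range also depends on how software handles a correlation estimate at its limit.

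A reader might also infer that correcting for twins always makes things worse, so that the t-test should simply be kept. That holds only under individual allocation. If twins are kept together, the t-test reaches 8.9% and a REML mixed model is closer to nominal.

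Finally, a logistic GEE has no finite estimate when one arm has no events. The chance of this is 1 − [1 − (1 − p)ⁿ]². With 26–30 per arm that is 38–46% at an assumed 5% event rate and 8–13% at 10%. But the protocol does not specify logistic GEE and names Fisher's exact test, so this is a side remark only.

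**Conclusion.** The concern holds in conditional form. If twins are enrolled and allocated individually, the methods named for the primary MDA test, used with their usual large-sample inference, could raise the type I error from 5% to about 6–14%. By method: exchangeable GEE about 7–14%, ML or REML mixed-model z about 6–10%, and independence GEE with sandwich errors about 5–7%. This rests on 52–60 infants, roughly 3–12 pairs, a within-pair correlation of 0.2–0.7, and complete, normally distributed data.

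Direction and mechanism are well supported. The exact size is not, since it depends on unstated choices and on software. The point should be settled before unblinding, but it does not show that the planned analysis must be invalid.

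**What to change.** In Statistical methods {20a}, drop GEE as an alternative for continuous outcomes and name one primary analysis: a linear mixed model with a random intercept for mother, fitted by REML, with Kenward-Roger standard errors and degrees of freedom. Add a re-randomisation test as support. It should repeat the allocation actually used, including whether twins were randomised separately or together, and Sequence generation {16a} should state which applies.

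The analysis plan should also say how Kenward-Roger inference is combined across the multiple imputations promised in {20c}, because the simulations did not cover imputed data. For uncommon binary outcomes, a re-randomisation test of the risk difference is an optional addition.

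The cost is one or two sentences and p-values slightly larger than uncorrected models would give. No extra infants or data are needed. Power is hardly affected: at a standardised difference of 0.8, with 52 infants and 7 pairs, Kenward-Roger and the t-test both had 81%. The planned difference is larger, at 8/7 = 1.14.

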### Interim analyses {21b}

No interim analyses have been planned as no problems likely to be detrimental to the participants are anticipated.

### Methods for additional analyses (e.g., subgroup analyses) {20b}

This is not applicable. There are no additional analyses planned.

### Methods in analysis to handle protocol non-adherence and any statistical methods to handle missing data {20c}

All randomized participants, regardless of protocol adherence, will be analyzed. Missing data will be handled with multiple imputation.

### Plans to give access to the full protocol, participant level-data, and statistical code {31c}

No later than 3 years after the end of the study (follow-up and statistical analysis phases included), we will deliver a completely de-identified dataset to an appropriate data archive for sharing purposes.

## Oversight and monitoring

### Composition of the coordinating center and trial steering committee {5d}

The coordinating center staff comprises neonatologists and child neuropsychiatrists responsible for patient enrollment and the assessment of clinical outcomes, and laboratory staff, researchers, and data analysts responsible for storing and providing placebo and ME to neonatologists, measuring biomarkers, collecting data, and compiling CRFs and the database. Together, all these staff members will coordinate the activity of the other physicians and researchers from the participating center.

The steering committee (SC) is composed of the PIs from each center and the “Support to Research Staff”. The SC’s duties are to oversee the advancement of the study, identify problems, and implement appropriate corrective measures.

### Composition of the data monitoring committee, its role and reporting structure {21a}

In our hospitals, we have dedicated data monitoring personnel who support the institutional ethics committees and PIs and Co-PIs; we refer, in particular, to the ECQT at the coordinating center. The said ECQT is external to the planned study and will actively monitor and audit the same through to the end of the follow-up. The personnel of the data monitoring committee (DMC) will monitor the ongoing study at regular intervals (twice a year).

Moreover, we declare that we have no sponsor. The planned trial is a spontaneous study and we have no competing interests.

